## Abstract

**Background:**

Occupational stress is associated with detrimental consequences that are addressed by mobile health (mHealth) solutions. Previous developments of apps for occupational stress have not yet fully exploited the potential of multilevel diagnostics through the integration of wearable sensors for interventions. Personalizing mHealth approaches in terms of intervention time and content, which requires the use of artificial intelligence, is the next logical developmental step. The "Relax" approach developed a corresponding prototype of an app-wearable system, which will be evaluated for effectiveness in terms of stress reduction and usability.

**Objective:**

This study protocol describes an evaluation study used to test the effectiveness and usability of the Relax approach.

**Methods:**

The evaluation study was designed as a 2-arm randomized trial with 2 phases, each with a 3-week intervention period. In both phases, employees were required to use the app to record daily stress and to wear a wearable sensor to measure heart rate variability. The app offered interventions based on algorithms, which altered the probability of their selection after learning from the data, thereby personalizing the user experience. In the second phase of the study, the sample was divided into 2 groups, varying the degree of personalization of the app. To analyze effectiveness, a 2-factorial mixed within-between design will be applied to compare the outcomes between both groups as well as in a pre-post comparison. In addition, exploratory analyses of the usability of the approach are planned.

**Results:**

The study was conducted during the spring and summer of 2024, with a total of 46 participants enrolled, and is ready for data analysis.

**Conclusions:**

The Relax approach, including a number of factors related to personalization that have not yet been incorporated into mHealth in current research, will provide new insights into the next steps of advanced mHealth solutions. Limitations of the study design, such as the lack of a control group and the sample representativity, have to be addressed.

**Trial Registration:**

Open Science Foundation 10.17605/OSF.IO/MYRD9; https://osf.io/myrd9

**International Registered Report Identifier (IRRID):**

DERR1-10.2196/68012

## Introduction

### Occupational Stress

For employees, work has the potential to be the most significant source of stress in their life. The working environment, which is often characterized by deadlines, role requirements, uncertainties, and time constraints, can be particularly stressful [1]. When stress is perceived as matching one’s abilities and motivations optimally, it can be referred to as “eustress” or a “flow experience” [2] and is characterized by positive emotions and high performance [3]. The term “distress,” which will henceforth be referred to simply as “stress,” describes the harmful type of stress that cannot be easily managed by the individual. Chronic work-related stress has been demonstrated to have detrimental impacts on an individual’s emotional well-being and overall quality of life [4]. Loss of energy and efficiency, mental and physical strains, and absence from work owing to burnout or other forms of mental health impairments are common consequences of unaddressed stress [5-7]. The study by Nekoei et al [8] recorded the suspected economic costs attributable to burnout as >2% of the national labor income, which demonstrates a continuous increase in workloads and speaks of an “epidemic of burnout” [9] affecting all fields of occupation, although some of them, such as health care, school education, or geriatric care, are particularly affected [10,11].

The provision of health care for working people with regard to stress-related burdens remains fragmented. The study by Molek-Winiarska and Molek-Kozakowska [12] showed that less than half of the organizations they had addressed committed to provide stress management support for their employees. In recent years, there has been a notable increase in interest in digital health solutions [13]. The COVID-19 pandemic, which placed many employees in unanticipated stressful work conditions, has demonstrated the urgent need for person-centered health care in the occupational setting, which can be effectively delivered by digital means [14]. The domain of mobile health (mHealth) addresses this type of individual health care, wherein mobile apps are used to facilitate cost-efficient and low-threshold access to effective interventions [15]. As the smartphone can serve as a constant companion during working hours [16], the provision of close health support via smartphone apps is particularly advantageous.

A plethora of mHealth apps addressing work stress are available in commercial sectors, as well as in scientifically based products [17-19]. The apps in question are highly diverse and exhibit considerable variation in their efficacy. Most apps concentrate on microinterventions derived from cognitive behavioral therapy (CBT), encompassing relaxation techniques, meditation, psychoeducation, and cognitive methods [17-19]. It may take many trial-and-error attempts for an employee to select a suitable approach [20]. An offer from the employer themself would be a logical and straightforward solution, particularly given the individualized nature of work stress, which can vary considerably depending on the specific workplace context. Given the continued tendency to regard mental health issues as a taboo subject in professional contexts [21], it is evident that mHealth apps for occupational stress are typically addressed at the individual level through the use of the employee’s personal smartphone rather than through the direct involvement of the employer. However, these apps must be tailored to the specific needs of the individual employee in terms of the stress-inducing circumstances and modes of coping and intervention without being set up by the employer. Therefore, the customizability of the app is important in developing an mHealth app for individual occupational stress.

### Personalized mHealth for Work Stress

The relevance of personalized apps that provide interventions for occupational stress is emerging [22,23]. On the one hand, personalization can be achieved simply through the input of personal data, which is then processed by the apps to customize interventions. To illustrate, a user may personalize the app using demographic data or specify the notification behavior for the intervention offer [24,25]. In addition to developments in the area of personal input and settings, there have also been significant advances in recent years in the field of combining apps with more advanced diagnostic measurement tools. The technical advancements in the domain of mobile sensors, or “wearables” for short, have opened up the opportunity for unobtrusive measurement of individuals’ current conditions through the use of wearable devices [26,27]. In the realm of stress diagnostics and interventions, this is particularly advantageous, as it enables the unobtrusive determination of heart rate variability (HRV), which is defined as a significant and practical physiological indicator of stress, although not the only one [28,29].

A multilevel diagnostic approach, which incorporates subjective input and objective sensor data, can facilitate the development of mHealth solutions for occupational stress management [17,26]. Such solutions are personalized on the basis of real-time data, a process referred to as “just-in-time adaptive interventions” (JITAIs) [30]. In this context, both the timing of the intervention and the content of the intervention are adapted to the situation and individual and therefore are necessarily linked to real-time data from the individual [31]. The necessity for the integration of multilevel data, coupled with the considerable volumes of data amassed through the integration of apps and wearables, necessitates the involvement of algorithms and learning agents in the background [32]. The development of artificial intelligence (AI) has led to its adoption in numerous domains of human-machine interaction, with the objective of enhancing user experience and personalizing processes [33]. In addition to smart technology such as voice assistants, the deployment of AI in health care apps could pave the way for the development of personal health assistants.

### Recent Developments and Research

This approach to health assistants is still in its infancy in terms of research and product development. General mHealth interventions with unobtrusive wearables are on the horizon, and their effectiveness has already been confirmed by several studies [34,35]. However, there is still a lack of attention being paid to the specific field of occupational stress [26,36]. Some approaches focus on safety systems that use wearables to monitor physical risks such as temperature and analyze physical stress but do not take mental stress into account [37]. Other approaches that explicitly examine mental stress have yielded the development of numerous systems designed exclusively for monitoring one’s own stress levels [27]. These systems lack the capacity for active interaction, such as the implementation of interventions. A recent review of the literature reveals that although mobile apps and wearable devices for mental stress interventions are also being developed, in most cases, they are based on either one or the other tool [26]. Combinations of both tools, in which the evaluated data are dynamically integrated, remain a barely addressed approach.

mHealth biofeedback apps provide an opportunity for such interactions, thus facilitating personalized mHealth interventions for occupational stress. In this approach, some developments have used real-time sensor data to feed into the app, which then provides the user with feedback on their stress levels [38]. When such measurements and feedback are coupled with breathing interventions, users have the ability to influence their heart rate through controlled or guided breathing [22,39-41]. Such interaction with the app allows for personalized data processing and can be seen as a basic form of individualization. There was only one approach that offered other CBT interventions in addition to biofeedback units for work stress, but these did not use the sensor data [22], which means that the full potential of continuous condition monitoring is not realized. Another way to personalize interventions is to use personal (sensor) data to determine the content of the intervention, a module, or the timing of the intervention, according to the JITAI concept. This idea was realized in the approach by Winslow et al [42], where CBT interventions were selected according to previous stress indications and conceptualized in the studies by Clarke et al [43] and Luštrek et al [44].

When developing such approaches, it is important to consider their real-world applicability as potential health companions in the everyday lives of their users. The feasibility of such apps goes beyond the technical capabilities and is closely related to usability factors. A review of the literature on mHealth usability shows that privacy is a particularly important concern for mHealth users [45,46]. This is evidenced by the fact that users express discomfort with the digital storage of sensitive health data, such as cardiac data or irregularities, within nontransparent commercial products [47]. A lack of motivation to integrate mHealth approaches into personal routines could be a consequence. Motivation, acceptance, and adherence issues are recognized as challenges in the development of mHealth [48,49]. In addition, although developed for the general population, highly educated, younger, or middle-aged individuals might access and adopt them more frequently, thus showing another challenge in the development of usable systems [50].

### The "Relax" Approach

The "Relax" approach involves the development of a system for multilevel diagnostics of occupational stress, with the aim of using these data to personalize interventions. This approach addresses the shortcomings of existing developments in the domain of personalized mHealth for work stress and extends the status quo by gathering a broad range of data for an AI-driven system to identify the most personally appropriate interventions from a diverse pool of contemporary CBT and health approaches.

The system combines a smartphone app for monitoring both direct and indirect subjective stress-related data, as well as dispositional personal data, and wearable devices for the assessment of cardiovascular indications of stress. The subjective data were multilayered, with dispositional and demographic characteristics serving as the basis for an individual profile for further personalization, as well as continuous data about current experiences that the AI would use to gain insight into the individual’s daily life. The data obtained from the sensors covered the area of objective stress measurement. The agent, trained with personal and stress-related data, was not only to determine the timing of an app-delivered intervention on an individual basis. In addition, the agent should select an individually tailored intervention that is as appropriate as possible at this predetermined point in time. Thus, the Relax project was planned to address the research on the development of JITAIs in mHealth for occupational stress in an advanced way. The concept of this approach, with its complexity and AI-driven personalization in the context of psychological support for work stress, addresses the existing gap in the field.

However, at the time of the evaluation, the system had not yet reached the final stage of development, that is, not all planned technical functions had been integrated. Regarding just-in-time quality, the functionality of the trigger system was limited to the essential function of triggering an intervention at a predetermined threshold of personal stress. This intervention has its adaptive quality in that the participants had to navigate through a predefined decision algorithm, in the form of a decision tree, when a stress event was detected to be offered an appropriate intervention in terms of situational fit. The specific probability of selection could be influenced and thus personalized by the participants through feedback ratings.

The pathways of the tree were represented by a series of successive questions about the experience of the current stress event. These were answered personally, resulting in increasingly specialized questions until, at the end, an intervention was delivered that was suitable for the input. The possible interventions from the repertoire were not exclusive per pathway, allowing for a wide range of interventions per pathway with different probabilities. The system decided which single intervention to offer the user based on the probabilities. The probabilities could be influenced by how the participants rated the intervention after it had been presented. Consequently, following a sufficient period of use, the probabilities of the interventions should be strongly modified on an individual basis, thereby reflecting the personal preferences for the interventions that are perceived to be personally most effective.

### Research Questions

This study aims to evaluate the prototype developed to date. The central research question of this evaluation is the effectiveness of the prototype in terms of the amount of stress reduction achieved by the participants. It is hypothesized that the greater the degree of personalization offered, the greater the reduction in stress. In addition, it was expected that all individuals would more or less experience an overall reduction in stress as a result of using the prototype. In addition to effectiveness, questions of usability and feasibility were addressed because of the pilot nature of the project approach and the research stage of the prototype at the time of the study. No hypotheses were formulated here, as the corresponding data were collected for exploratory purposes.

## Methods

### Study Design

The study used a 2-arm randomized controlled design, comprising 2 experimental groups with varying levels of intervention. In a field design, participants applied the intervention in their natural (occupational) environment. Two 3-week study periods were conducted, with all participants receiving the same intervention in the first 3-week phase (P1) and, after a 3-week break, being allocated to 1 of 2 groups in the second 3-week phase (P2). This resulted in a within-subject comparison in the pre-post design as well as between-subject comparisons between both experimental groups. The within-subject design consisted of the collection of time series data enabled by the continuous daily measurement of variables. Subjective data on experiences and stress levels were collected daily in the morning and evening, as well as at least twice during the day, via the app. Continuous physiological data were also collected via wearing a sensor. In contrast, the between-subject design comprised 3 measurement points: before P1 (T1), between P1 and P2 (T2), and after P2 (T3). At these times, web-based questionnaires about chronic stress and various usability aspects of the wearable app system were submitted via a web-based survey platform. The break was used to improve the mobile app based on user feedback, split the participants into the experimental groups, train the models for automated stress detection based on the HRV and questionnaire data recorded in P1, and implement the weight adjustment mechanisms for personalized intervention delivery.

### Ethical Considerations

The study design and conditions were initially approved in advance by the Ethics Committee of the University of Salzburg (EK-GZ 25/2023). Following minor alterations to the study design, including adjustments to the study duration, study period, the exclusion of a second sensor, and the reduction of the number of participants, an amendment was approved by the same committee (EK-GZ 25/2023 amendment). After data collection, a preregistration for hypothesis testing was performed (osf.io/myrd9). Due to the unpredictable nature of the study and the technical adjustments required during implementation, prospective preregistration was not performed.

Before completing the screening questionnaire, respondents were informed of the purpose of the data collection in order to provide informed consent. Those who were screened positively were informed of the acceptance of their registration via the email address they had provided. Those who were screened negatively were informed of the exclusion immediately after the screening. After the conclusion of the registration period, the final registration confirmations were sent out to all individuals included in the optimally balanced sample. Subsequently, the positions of those who had dropped out before the commencement of the study were filled by new participants until shortly before the study began. The identities of the participants were pseudonymized before the collection of study data. Participants were provided with an individual, reproducible code comprising questions on personal characteristics that could not be traced back [51]. The identity was only traceable by means of a coding list, which was kept by the study management and was only consulted in serious technical cases, dropouts or when checking whether the level of participation was sufficient to apply for the proposed compensation. Interested individuals were informed about the financial compensation worth €180 (US $204.86) (including the value in kind of retaining the study sensor). They could opt out at any point without negative consequences.

### Study Participants

The sample consisted of individuals who were of legal age and employed. Participants were required to possess a smartphone with a minimum Android operating system (version 7.0). In advance of the study, participants were required to demonstrate a sufficient level of knowledge of the German language, equivalent to that of a native speaker, as well as normal or corrected-to-normal eyesight. To be eligible for inclusion in the study, participants were asked to indicate that they had sufficient time to use the app daily during the study period, including having the opportunity to use the app every 3 to 4 hours. In addition, participants were only eligible if they had a regular working day that was not interrupted by holidays, significant changes in employment status, or travel during the study period.

Individuals who met the following criteria were excluded from the study: those with irregular work routines during the study period (eg, irregular night shifts), cardiovascular diseases, or atypical menstrual cycle complaints in women, those with upcoming medical interventions during the study period, and those with a diagnosed severe mental disorder or undergoing psychotherapy or psychopharmacotherapy. Inclusion and exclusion criteria were clarified by self-report unless the information was obviously evaluable. There were no restrictions regarding the location of participants in German-speaking countries or their occupational fields. The participants were able to communicate with the study team via online correspondence, including email and telephone.

### Sample Size

The optimal sample size for the central analysis of main effects was calculated using an a priori power analysis with G*Power (version 3.1) [52]. With an α value of .05, a power of 1-β=0.80, and a desired effect size of Cohen *d*=0.5, this resulted in a recommended sample size of 31. The sample size was increased in the study to the maximum number of participants that could be financed, which was 50 individuals. This resulted in a maximum of 25 (50%) individuals per experimental group.

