### Statistical Analysis

To statistically analyze the central evaluation questions of the prototype developed in the Relax project in terms of its efficacy in reducing stress in the workplace, different models will be constructed. First, the difference between the groups and thus the degree of individualization by the app will be determined. Second, the pre-post design will be used to ascertain whether the individuals exhibited a reduction in stress over time. These 2 approaches will use all stress-relevant outcomes to make assertions about the work stress of the individuals, namely the emotional states, self-reports on chronic stress as well as distress and eustress, and the physiological parameters. Linear mixed models will be used for the effectiveness analyses.

To address the usability and feasibility of the prototype, the data obtained from the satisfaction and usability scales will be used. These will also be analyzed between the groups and in the pre-post design. Exploratory analyses will test the secondary outcomes for possible effects. Additional moderation and mediation analyses will be possible here, in which the variables from the demographic and profile surveys could also be used. It is anticipated that the qualitative data from the user feedback will provide information about the specific background of the participants’ usability ratings.

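### The N=31 power calculation fits the within-person change, not the local-versus-global comparison listed first, where 46 to 50 participants give about 38% to 41% unadjusted two-sided power

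*Protocol article*

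**What the plan says.** The Sample Size section of the protocol article describes one calculation: "The optimal sample size for the central analysis of main effects was calculated using an a priori power analysis". Its inputs are "With an α value of .05, a power of 1-β=0.80" and "a desired effect size of Cohen *d*=0.5", and "this resulted in a recommended sample size of 31". The number was then raised to 50, the most that could be financed, or at most 25 per experimental group. The Results section reports 46 participants.

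The abstract describes a two-factor mixed within-between analysis. Under Research Questions the first hypothesis is about the groups: "It is hypothesized that the greater the degree of personalization offered, the greater the reduction in stress". The Statistical Analysis section keeps that order: "First, the difference between the groups and thus the degree of individualization by the app will be determined". The pre-post change comes second, and linear mixed models are planned for both. No other power figure is given.

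**The concern.** In a design with a group factor and a time factor, the main effects include the group effect. A single power statement for main effects, followed by a larger sample expressed per group, can therefore be taken to cover local versus global. If it does not cover it, the trial lacks the stated power for its first hypothesis. The analyses had not been run when the article was written. A non-significant group difference, set beside a stated 80% power, could then be taken to show that greater personalization adds nothing.

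**Working it through.** **Inputs from the article.** Alpha .05, power .80, d=0.5, stated N=31 and maximum N=50 (25 per group), all from Sample Size; achieved N=46, from Results. **Assumptions.** A 23/23 split at N=46 (only the total is given), both one- and two-sided tests (sidedness is not stated), and a range of baseline correlations (none is stated).

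**1. The plan's own figure, as a within-person effect.**
- Normal approximation, two-sided: n = (1.960 + 0.842)² / 0.5² = 7.85 / 0.25 = 31.4, so 32 rounded up.
- Paired t-test, noncentrality d√n, n−1 degrees of freedom: 34 two-sided (power 0.808) or 27 one-sided (0.812). At n=31 the power is 0.768 or 0.859.
- Wilcoxon signed-rank test in G*Power's relative-efficiency method (n replaced by n × A.R.E. in the paired-t formula). Two-sided with a logistic parent, A.R.E. = π²/9 = 1.097: power 0.794 at n=30 and 0.808 at n=31, so 31. One-sided with the minimum A.R.E. of 0.864: 0.797 at n=30 and 0.809 at n=31, so 31.
- Repeated-measures ANOVA, within effect, two occasions, f=0.25, λ = f²·N·2/(1−ρ): 34 at ρ=0.50 and 31 at ρ=0.55.

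So 31 is an attainable result for a within-person effect under several settings. Which one was used is not stated.

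**2. The same inputs for local versus global, unadjusted.** Two-sample t-test, noncentrality d√(n₁n₂/(n₁+n₂)), n₁+n₂−2 degrees of freedom.
- Normal approximation: n per group = 2 × 7.85 / 0.25 = 62.8. The exact t calculation gives 64 per group, or 128 in total. One-sided it gives 51 per group, or 102 in total.

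| N (split) | Noncentrality | Two-sided power | One-sided power |
|---|---|---|---|
| 31 (15/16) | 1.391 | 27% | 39% |
| 46 (23/23) | 1.696 | 38% | 51% |
| 50 (25/25) | 1.768 | 41% | 54% |

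- Detectable d at 80% power, two-sided: 0.84 at N=46 and 0.81 at N=50.
- 95% confidence interval half-width at N=46: 2.015 × √(4/46) = 0.59 SD.
- As the between-group main effect of a repeated-measures ANOVA (f=0.25, ρ=0.5), λ = f²·N·m/(1+(m−1)ρ) gives 97 with two occasions and 86 with three.

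**3. With baseline adjustment.** One baseline covariate with correlation r turns d into d/√(1−r²), with N−3 degrees of freedom.

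| Assumed r | Two-sided power, N=46 | Two-sided power, N=50 |
|---|---|---|
| 0.3 | 41% | 44% |
| 0.5 | 48% | 52% |
| 0.7 | 64% | 68% |
| 0.8 | 79% | 82% |

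**4. The pre-post question.** A two-sided paired t-test at d=0.5 has 91% power at N=46 and 93% at N=50.

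**The case against.** **The planned model is not a t-test.** This stands in part. Linear mixed models are planned and the first phase precedes randomization, so a baseline is available. The hypothesis is also directional. The 38% to 41% therefore describes an unadjusted two-sided comparison and is not a fixed property of the trial. But one-sided testing without adjustment reaches only 51% to 54%, and adjustment brings two-sided power to about 80% only near r=0.8. The article states no correlation on which to rest that gain.

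**G*Power's group-by-time interaction also gives numbers near 31.** With f=0.25 and two occasions it gives 34 at ρ=0.50 and 31 at ρ=0.55. The text, however, says main effects, and the effect scale differs. With two groups and two occasions, f=0.25 puts each cell 0.25 SD from additivity, so the groups differ in change by 4 × 0.25 = 1.0 SD. At ρ=0.5 the SD of change is √(2(1−0.5)) = 1 SD, so this is a between-group d of 1.0, twice the stated 0.5.

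**The article is cautious.** It calls the study a pilot, promises only a first impression of effectiveness, and names the lack of an untreated control group. It never says in so many words that the group comparison has 80% power. This lowers the weight of the point. The caveats are general, though, and none concerns the power of the randomized comparison.

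**A stronger reading to avoid.** A reader who tries only the paired t-test (34 or 27) might infer that 31 is a miscalculation and should become 34. The documents do not support that, since the settings in step 1 return exactly 31. Nor is a full list of G*Power inputs something a condensed article must carry. The test needs naming here because, without it, the power statement reads as covering effects for which it does not hold.

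**Conclusion.** The point holds in this form: the single power statement, worded for main effects, fits the within-person change and does not give 80% power at d=0.5 for local versus global, the comparison placed first. Unadjusted two-sided power there is about 38% at N=46 and 41% at N=50, with detectable differences of about 0.84 and 0.81 SD. The total needed is 128 two-sided or 102 one-sided. These figures assume equal groups and a between-group d in outcome SD units. Power is higher with a one-sided test or baseline adjustment, as shown. No arithmetic error in 31 is established. The point is worth correcting but is not of the gravest kind: data collection is complete, the pre-post question is well served, and the article already presents its effectiveness results as preliminary.

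**What to change.** In the Sample Size section, state that the N=31 calculation concerns the within-person effect, and name the test, its sidedness and the type of d. Leave 31 in place unless the authors' own record of the calculation shows otherwise. Add a separate sentence for local versus global giving the power at d=0.5, or the detectable difference, at the achieved group sizes, with the sidedness and any baseline correlation assumed. State that this comparison will be reported as an estimate with a confidence interval, and that a non-significant result will not be taken as showing no benefit of personalization.

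The cost is a few sentences. The stated power becomes less favourable for the first hypothesis. No additional participants are needed, and neither the data nor the planned models change.
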